#### Protocol non-adherence and missing data

Participants withdrawing from the study and reasons for withdrawal will be analyzed. Characteristics of participants and non-participants will be compared. Multiple imputation will be used to handle missing data. The primary analysis set is the FAS for ITT analysis. The secondary analysis set is the PP set. Drop-outs will be replaced with reference-based multiple imputation – “Jump to reference” [60]. This method is conservative in handling the attrition bias. Other methods will be applied as sensitivity analyses (e.g., LOCF, BOCF, and total mean replacement). The estimand will be the effect achievable in patients with an affinity for apps vs. TAU. Patients who are symptom-free prior to completion of the study are free to discontinue the therapy. These patients are not dropouts.

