## Interventions

### Explanation for the choice of comparators

The control group (control group [CG]) will undergo TAU, which is physiotherapy. No therapy cannot be justified, because patients may need therapy. Control patients will receive a physiotherapy prescription and make appointments with a physiotherapist of their choice on their own. No influence will be exerted on timing and possible waiting time, so that these correspond to the TAU procedure.

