### Relevant concomitant care permitted or prohibited during trial

With the exception of the exclusion criteria, other accompanying therapy will be allowed and not influenced by the therapy with the app. Rescue therapy is indicated in the event of life-threatening progression of the underlying disease or a severe deterioration in quality of life. At the end of the clinical trial, the treatment of a patient will not necessarily be complete in all cases. In the IG, the patient can continue to use the app for up to 12 months. In the CG, the use of the app will be available to every patient free of charge after 12 weeks and up to 12 months. Arrangements will be made for additional health care for subjects who suffer from an AE.

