### Sample size

The proposed sample size is 200, with 100 per group. The primary endpoint (VSS-sf-VER (German version of VSS-G) has a range of 32. Because no empirical data are available, 15% (IQWiG 2022) [59] of the range was chosen as a relevant effect, i.e., 5; the imputation methods are conservative, and the real effect has to have 6. The standard deviation of the change from baseline to week 12 is expected to be less than 12. To account for the reducing effect of replacing missing values or dropouts, a drop outs/imputations-addition is included, resulting in the final case number calculation.

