## Discussion

In the treatment of chronic vertigo physiotherapy is effective [7–9]. Its application, however, by a physiotherapist is often restricted to a limited number of sessions. Adherence to home-based therapy is frequently insufficient, prompting the development of VH-90-D DTx [9, 11, 13–15]. This study aims to evaluate the DTx´s efficacy and safety. A further focus is on the comparative advantages of digital therapy including benefits for the patient, impact on quality of life, technological developments in rehabilitation, costs, and accessibility. The instruments used allow to investigate vertigo intensity, vertigo-induced loss of quality of life and handicap, disease improvement, vertigo associated stress, adherence barriers, health competence, and health decision-making competence. This trial protocol marks a confirmatory RCT (GEVE II) to investigate the efficacy and safety of DTx for vertigo by VH-90-D DiGA (Vertidisan®). VH-90-D DiGA is a medical device, standalone software, and a health app. DTx allows a multimodal approach and contains vestibular exercises that may be designated as ABEV stimulation exercises. The general effectiveness of vestibular exercises for the treatment of peripheral vertigo has been demonstrated by clinical evidence and is based on cerebral vertigo compensation (CVC) [40]. Recently, an own study of ABEV exercises was completed and served as a foundation for the current trial [61]. In the study, a retrospective analysis of data from a cohort of 104 intra-individually controlled patients demonstrated that vertigo-specific ABEV stimulation exercises are significantly effective in reducing peripheral vestibular vertigo. Cohen's d showed large effect sizes. Thus, the data provide high real-world effectiveness at Oxford Evidence Level 2a and Grade B. From this intra-individually controlled data alone, we can infer statistical probability and clinical effect size but not necessarily the causality of the ABEV stimulation exercises. Furthermore, the published study has some limitations that may affect the internal and external validity of the results. The enrollment followed a consecutive selection mechanism. Moreover, a relevant loss-to-follow-up was noted, which is typical for retrospective studies. The drop-outs may produce bias.

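### Jump-to-reference is called conservative without condition, but the reference is active physiotherapy, so the claim fails if app dropouts do worse than physiotherapy patients; no named sensitivity analysis isolates that case

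*Protocol article*

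**What the plan says.** Under Protocol non-adherence and missing data, the protocol article sets the primary method: "Drop-outs will be replaced with reference-based multiple imputation – “Jump to reference". It then says, with no condition attached, "This method is conservative in handling the attrition bias". For sensitivity it adds "Other methods will be applied as sensitivity analyses (e.g., LOCF, BOCF, and total mean replacement". The estimand is given in one sentence, "The estimand will be the effect achievable in patients with an affinity for apps vs. TAU", which does not say how the outcome after stopping the app is to be treated.

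The Sample size section uses the same premise to move from a relevant effect of 5 points to a larger true effect: "the imputation methods are conservative, and the real effect has to have 6".

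The reference arm is active. Under Explanation for the choice of comparators: "The control group (control group [CG]) will undergo TAU, which is physiotherapy". The Discussion states "In the treatment of chronic vertigo physiotherapy is effective". Nothing in the article says that a patient who abandons the app then receives physiotherapy. The section on concomitant care says only that "other accompanying therapy will be allowed and not influenced by the therapy with the app".

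**The concern.** J2R is usually called conservative because an experimental-arm dropout is given the course of the reference arm. With a placebo or untreated reference, that means losing the treatment benefit. Here the reference is a treatment, so the dropout is credited with the average benefit of a physiotherapy course that he or she may not have had. Whether this is cautious depends on how app dropouts actually fare, and the article treats the answer as settled.

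At stake is the primary confirmatory comparison, which also opens the ordered sequence of six secondary tests. If app dropouts do worse than the average control patient, the primary estimate leans towards the app. A reader who relies on the word conservative, and on sensitivity analyses that happen to agree, would not know it.

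**Working it through.** **Inputs from the protocol article.** Superiority, two-sided 5% level; 100 per group; relevant effect 5 points (15% of 32 = 4.8); true effect needed 6; SD of change below 12.

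**Assumptions, because the text shown gives no figures.** Mean improvement under physiotherapy, mu_c: 2, 4 or 6 points. Completer difference: 6 points, so app completers improve by mu_e = mu_c + 6. Dropout shares d_e (app) and d_c (control): one-sixth in both arms, 30% against 10%, and 10% against 20%. Differences are on an improvement scale, so positive favours the app.

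**The plan's own figures.** At SD 12, a difference of 5 needs 91 per arm for 80% power (102 after 10% dropout); a difference of 6 needs 85 per arm for 90% power (100 after 15% dropout). Several pairs of assumptions lie near 100 per group, so that figure is neither confirmed nor refuted. The step from 6 to 5 is what J2R dilution gives at d_e = 1 − 5/6 = 16.7%.

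**Formulas for the expected difference**
- J2R: (1 − d_e)·mu_e + d_e·mu_c − mu_c = (1 − d_e)(mu_e − mu_c).
- App dropouts return to baseline, control dropouts keep mu_c: (1 − d_e)·mu_e − mu_c.
- BOCF in both arms: (1 − d_e)·mu_e − (1 − d_c)·mu_c.

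Subtracting:
- J2R minus the return-to-baseline case = d_e·mu_c.
- J2R minus BOCF = mu_c·(d_e − d_c).

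**Where J2R is conservative.** Against missing-at-random, a completer difference of 6 becomes (5/6)·6 = 5.0 at one-sixth dropout and 0.7·6 = 4.2 at 30%.

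**Where it is not.** Credit d_e·mu_c to the app, in points:

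| d_e | mu_c = 2 | mu_c = 4 | mu_c = 6 |
|---|---|---|---|
| 1/6 | 0.33 | 0.67 | 1.00 |
| 0.30 | 0.6 | 1.2 | 1.8 |

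With mu_c = 4 (mu_e = 10), the differences in the return-to-baseline case are (5/6)·10 − 4 = 4.33 and 0.7·10 − 4 = 3.0, against J2R values of 5.0 and 4.2.

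**The credit can vanish.** If dropouts in both arms return to baseline at an equal share of one-sixth, the difference is (5/6)·10 − (5/6)·4 = 5.0, which is the J2R value.

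**What the named sensitivity analyses would show (mu_c = 4)**

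| Dropout app / control | J2R | BOCF | Total mean replacement | App dropouts to baseline, controls keep mu_c |
|---|---|---|---|---|
| 1/6 / 1/6 | 5.0 | 5.0 | 5.0 | 4.33 |
| 30% / 10% | 4.2 | 3.4 | 4.72 | 3.0 |
| 10% / 20% | 5.4 | 5.8 | 5.08 | 5.0 |

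At equal dropout, BOCF and total mean replacement agree with J2R whatever happens to app dropouts. At 30% against 10%, BOCF shows 0.8 of the 1.2 points; total mean replacement moves towards the app. When control dropout is higher, BOCF moves towards the app.

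LOCF depends on when patients leave. A week-2 score has a one-month recall, so about (30 − 14)/30 = 53% of its window precedes treatment, which pulls it towards baseline. A week-6 score has no such overlap. LOCF, too, is applied to both arms.

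**Effect on the error rate.** Simulation of J2R with Rubin's rules (4,000 runs, 10 imputations, 100 per arm, no covariate), assuming SD 8, mu_c = 4, no true difference, app dropouts at baseline and control dropouts at mu_c: false superiority was 0.048 at one-sixth dropout in both arms and 0.086 at 30% against 10%, where 0.025 is nominal. A repeat run gave 0.048 and 0.077.

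**The case against.** The best defence is that the word has a sound meaning here. Against missing-at-random, with the app truly better, J2R does dilute the effect, and the step from 6 to 5 fits that reading. This stands: the statement lacks a condition and is not simply false.

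Second, the overstatement needs an asymmetry, with app dropouts losing everything while control dropouts keep the physiotherapy benefit. No section supports that as fact. App dropouts may keep some benefit or use other permitted therapy, symptom-free stoppers are not counted as dropouts, and physiotherapy here is self-arranged with whatever waiting time arises. This also stands: the bias is possible, not shown. A reader might infer that J2R necessarily favours the app in this trial; the article does not support that.

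Third, a reader might infer that the listed sensitivity analyses cannot reveal the problem. That is too strong. BOCF gives app dropouts zero change. It shows part of the credit when app dropout is higher, and all of the excess if control dropouts also return to baseline. It is blind at equal dropout.

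Fourth, the list is given as examples in a condensed article, and further analyses may be in an analysis plan not shown. So the absence of a tipping-point analysis is not itself a fault. What remains is the unconditional claim, which is stated here and used in the sample size.

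**Conclusion.** The claim that J2R is conservative needs a condition. It holds relative to missing-at-random when the app is better than physiotherapy; it fails if app dropouts do worse than physiotherapy patients. In the adverse case (app dropouts back at baseline, control dropouts at the control mean) the overstatement is 0.33 to 1.0 points at one-sixth dropout and 0.6 to 1.8 points at 30%, against a relevant effect of 5. These sizes rest on an assumed physiotherapy improvement of 2 to 6 points and assumed dropout shares. The error rates also rest on an assumed SD of 8, where the article gives only an upper bound of 12.

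The named single-value methods change both arms by one rule, so none isolates the assumption about app dropouts. This is a correction of a stated property plus an inexpensive added analysis. It does not invalidate J2R as the primary method.

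**What to change.** 1. In Protocol non-adherence and missing data, and in Sample size, qualify the claim: J2R is conservative relative to missing-at-random when the app is better than treatment as usual, and not if app dropouts fare worse than physiotherapy patients.
2. Keep J2R as primary and keep LOCF, BOCF and total mean replacement. Removing published sensitivity analyses would weaken pre-specification, and BOCF is informative when app dropout is higher.
3. Add a multiple-imputation analysis in which app-arm dropouts return to their own baseline and control dropouts are imputed under missing-at-random.
4. Add a delta-adjusted tipping-point analysis that worsens the imputed values of app-arm dropouts only, step by step, and reports the delta at which significance is lost.

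The Trial status section says the article was re-submitted after the study closed. If the data are already unblinded, label items 3 and 4 post hoc. The cost is wording plus about a day of programming, with no new data. The downside is that the reported robustness may look less favourable.

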### Statistical methods

For descriptive statistics, usual methods will be used for quantitative variables (i.e., means, medians, standard deviations, quartiles, maximum and minimum). For qualitative variables, absolute and relative frequencies will be determined. Furthermore, 95% confidence intervals (CIs) will be calculated where appropriate. Analysis of covariance (ANCOVA) will be used for the analysis of changes from baseline with baseline as a covariate and treatment group as a factor. No formal pre-tests of normality or homoscedasticity are planned; the range of the score data (changes from baseline) is limited without extreme skewness; the homoscedasticity of the 2 groups of changes is given under the assumption of no treatment effect. The sample sizes of about 100 per group make this simple ANCOVA with 1 factor (group) and 1 covariate (baseline) asymptotically robust even in the case of not normally distributed data. Wilcoxon tests will be used for sensitivity analyses. For confirmatory statistics, the following a priori-ordered tests will be used:

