#### Primary confirmatory endpoint

Group comparison of the change in VSS-sf-VER from baseline to Week 12. The primary hypothesis to be tested is the equality of the VSS-sf-VER change against the alternative of the superiority of VH-90-D vs. TAU with a two-sided significance level of α = 5%. ANCOVA with experimental group as factor and baseline as covariate and sensitivity analysis with a Wilcoxon rank test stratified by baseline values will also be carried out.

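### Total mean replacement is a weak missing-data check: it nearly repeats the complete-case test, with a diluted estimate and an interval narrower than with no data missing

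*Protocol article*

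**What the plan says.** The section Protocol non-adherence and missing data sets the primary approach: "Drop-outs will be replaced with reference-based multiple imputation", specified as jump to reference and described as conservative. It continues: "Other methods will be applied as sensitivity analyses (e.g., LOCF, BOCF, and total mean replacement". It does not say over which patients the total mean is taken or how the result is to be read.

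The model is fixed under Statistical methods: "Analysis of covariance (ANCOVA) will be used for the analysis of changes from baseline with baseline as a covariate and treatment group as a factor". The Sample size section says "The proposed sample size is 200, with 100 per group", takes 5 points as the relevant effect and an SD of change below 12, and expects dilution: "the imputation methods are conservative, and the real effect has to have 6". The estimand sentence reads: "The estimand will be the effect achievable in patients with an affinity for apps vs. TAU".

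**The concern.** A missing-data sensitivity analysis should show whether the conclusion survives a different, plausible assumption about the patients who left. Filling every gap with one constant is a single imputation. The filled values carry no arm difference and almost no spread, yet they count as observed patients. The estimate and its standard error should then shrink together, which leaves the complete-case test almost unchanged.

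What is at stake is the reading of the report. A statement that the result also holds under mean replacement would sound like independent support, but it would add little to a complete-case analysis. The printed interval would also look more precise than a trial that lost nobody.

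**Working it through.** **Inputs from the article.** 100 per arm; SD of change 12 (given as an upper bound); effect 5, which is 15% of 32 = 4.8 rounded up; ANCOVA on baseline; two-sided 5%. The Sample size section asks for a real effect of 6 to show 5, and 1 - 5/6 = 16.7% is the dilution this implies.

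**Assumptions.** Missing share m of 10%, 16.7% or 30%, equal in both arms and at random; baseline-change correlation -0.3.

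**Algebra without the covariate, total mean taken over both arms.**
- Estimate: (1 - m) x complete-case difference. At 16.7%: 0.833 x 5 = 4.17.
- SE with nothing missing: 12 x sqrt(2/100) = 1.70.
- SE for complete cases: 12 x sqrt(2/83.3) = 1.86.
- Within-arm variance after filling: (1 - m) x (SD² + m x effect²/4) = 0.833 x (144 + 1.04) = 120.9. SE = sqrt(2 x 120.9/100) = 1.55, close to 0.833 x 1.86.
- t: 4.17/1.55 = 2.68 against 5/1.86 = 2.69 for complete cases.
- Coverage of the undiluted 5: the bias is 0.833, or 0.833/1.555 = 0.536 SE. Coverage = Φ(1.96 - 0.536) - Φ(-1.96 - 0.536) = 0.917. The same steps give 0.939 at 10% and 0.817 at 30%.

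**Simulation with baseline ANCOVA** (6,000 trials per setting, effect 5; estimates shown as size of benefit):

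| Missing | Analysis | Estimate | Reported SE | Sampling SD | CI width | Covers 5 |
|---|---|---|---|---|---|---|
| 0% | all data | 5.00 | 1.62 | 1.62 | 6.40 | 95% |
| 10% | complete case | 5.00 | 1.71 | 1.71 | 6.75 | 95% |
| 10% | total mean | 4.50 | 1.55 | 1.54 | 6.11 | 94% |
| 16.7% | complete case | 5.01 | 1.78 | 1.74 | 7.02 | 96% |
| 16.7% | total mean | 4.16 | 1.50 | 1.46 | 5.90 | 92% |
| 30% | complete case | 5.03 | 1.94 | 1.94 | 7.68 | 95% |
| 30% | total mean | 3.51 | 1.38 | 1.38 | 5.46 | 81% |

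The t statistic correlates 0.99, 0.99 and 0.98 with the complete-case one, and the significance decision agrees in 98%, 97% and 96% of trials. With no true effect, total mean replacement rejects in 4.6%, 4.9% and 5.4%.

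**Against the primary method** (true effect 6, correlation -0.5, 1,500 trials). At 16.7% missing, total mean replacement and jump to reference both average 4.99, with interval widths of 5.47 and 6.36. They reject in 94.5% and 91.0% of trials. At 30% missing they reject in 89.3% and 73.9%.

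**Reaction to poor outcomes in drop-outs.** Suppose 30% of the app arm and 10% of controls are lost, and app drop-outs end 5 points worse than control. The true effect over all patients is 0.7 x 6 - 0.3 x 5 = 2.70. Full data would reject in 42% of trials, jump to reference in 78%, total mean replacement in 93% and complete case in 95%.

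**Other reading: within-arm mean.** The estimate is not diluted, but the SE is too small by about (1 - m). Type I error is then about 2 x Φ(-1.96 x (1 - m)): 7.8%, 10.2% and 17.0%. Simulation gives 7.8%, 10.6% and 17.8%.

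**The case against.** A reader might infer that the standard error from total mean replacement is simply wrong, so that its interval is invalid for any target. The check does not support that for the both-arms mean. Reported SE and sampling SD agree (1.50 against 1.46 at 16.7%, 1.38 against 1.38 at 30%), and type I error is near 5%. The undercoverage arises because the estimate is pulled toward zero inside an interval that does not widen for lost data.

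Coverage also depends on the target. The Sample size section expects dilution, and jump to reference dilutes as well: at 30% missing with a true effect of 6 it covers the undiluted effect in only 88.8% of trials. If app drop-outs truly lose the whole effect, total mean replacement covers that diluted effect in about 95%. At 10% missing the loss of coverage is slight.

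The shrinkage is toward no effect, so under equal random loss the size of benefit is not exaggerated. The method is one of three examples in an open list, a stratified Wilcoxon sensitivity test is planned too, and a full analysis plan may define the term. All of this stands and limits the weight of the point. It does not make total mean replacement a useful check, since under either reading it is uninformative or miscalibrated.

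**Conclusion.** The point holds as a cheap improvement to the sensitivity analyses. Read as the mean over both arms, total mean replacement nearly repeats the complete-case test. It gives an estimate diluted by about the missing share and an interval narrower than with no missing data. Coverage of an undiluted effect of 5 is about 94%, 92% and 81% at 10%, 16.7% and 30% missing. Read as the within-arm mean, it inflates type I error to about 8% to 18%.

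These figures rest on SD 12, a baseline-change correlation of -0.3 and equal random loss. The dropout shares are assumptions, with 16.7% only implied by the 5 against 6. With a correlation of -0.5 or unequal loss the link to the complete-case test is looser: t correlations go down to 0.94 and agreement of decisions to 91%.

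A reader might also infer that the confirmatory result or the sample size is compromised. Neither depends on this analysis.

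**What to change.** In Protocol non-adherence and missing data, replace total mean replacement with the same multiple-imputation model run without the jump, that is, under missing at random within each arm, pooled by Rubin's rules. Include the week 2 and week 6 scores where they were collected. With baseline alone, such a model would again sit close to complete cases. If a complete-case ANCOVA is wanted, list it under that name.

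The Trial status section says the article was re-submitted after the study closed. The change should therefore be dated and labelled as such in the analysis plan or report.

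The cost is one line of wording and one further run of an imputation model that is needed anyway, with no new data. The interval will be wider than under mean replacement. If the intermediate visits add little, it will be near the complete-case width (7.0 against 5.9 points at 16.7% missing in the setting above), which reflects the information actually lost.

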#### Plans to give access to the full protocol, participant-level data and statistical code

The protocol, data, and statistical code that support the findings of this study will be available from the corresponding author, upon reasonable request.

### Oversight and Monitoring

#### External data monitoring committee, its role and reporting structure

An external data monitoring committee is established whose members are responsible for patient care in case of AEs, hazards, or device dysfunction.

